**Figure 2 F2:**
[figure not shown]
Components of the RE-HOPE intervention strategy. The strategy consists of four sequential components: a) active identification of individuals with hypertension through individual and community-based screening; b) referral to primary healthcare services with a cardiovascular risk management approach; c) training of the implementation team in the study protocol, tools, and procedures; and d) health counseling focused on treatment adherence, healthy lifestyles, and stress management. CHW, community health workers; CV, cardiovascular.

Home-based health counseling: CHWs will conduct home visits at months 1, 3, 6, 9, and 12 (Figure 3). Each visit will include an assessment of health education needs and a brief (approximately 20 min) structured counseling session on key hypertension-related topics. Counseling materials will be developed and validated by healthcare professionals with expertise in health sciences. CHWs will receive training before delivering the sessions for a Nurse whit high level education. The counseling sessions will cover the following topics:
Disease awareness: CHWs will explain the diagnosis of hypertension in clear, accessible language, emphasizing its importance and its relationship to cardiovascular disease.Medication adherence: Participants will be encouraged to take their medications daily, supported by tools such as pillboxes, medication cards, or reminders tailored to their preferences.Physical activity promotion: Participants will be advised to engage in at least 150 min of moderate-intensity or 75 min of vigorous-intensity physical activity per week, including isometric strength training (14).Reduced sodium intake: Participants will be counseled to limit their intake of processed and packaged foods while increasing their consumption of fruits, vegetables, and home-prepared meals.Reduced alcohol consumption: Limit alcohol intake to one drink per day for women and two drinks per day for men.Tobacco and vape cessation: CHWs will encourage participants to quit tobacco and vaping products.Stress and emotion management: CHWs will help participants identify stressors at home and suggest simple, comforting activities to manage stress.

**Figure 3 F3:**
[figure not shown]
Follow-up visit schedule. The intervention includes five scheduled follow-up visits over 12 months. At each visit, participants will receive health counseling, blood pressure measurement, weight monitoring, and a review of their pharmacological treatment. BP, blood pressure.

Healthcare provider training: The research team will train CHWs in standardized blood pressure measurement techniques, strategies to enhance medication adherence, the use of data collection tools, health counseling, and assertive community engagement. Ongoing training sessions will also be held for healthcare professionals and technicians at primary care centers receiving study participants. Topics will include hypertension detection and management based on World Health Organization (WHO)-recommended fixed-dose combination therapy algorithms (15). The training is provided by health professionals who serve as operational coordinator and others health professionals.

### Follow-up

CHWs will arrange appointments for home follow-up visits (months 1, 3, 6, 9, and 12), and blood pressure will be measured according to the standardized protocol. Additional data will be collected on anthropometric variables, physical activity habits, tobacco and alcohol use. The follow-up framework aligns with the guidelines of the International Society of Hypertension for hypertension management and the WHO guidelines (2, 15). Barriers to accessing antihypertensive medications and statins within the healthcare system will also be evaluated. If participants are found to have uncontrolled hypertension, they will be referred to their corresponding primary care center for medical evaluation and adjustment of antihypertensive therapy. In cases of critically elevated blood pressure (>180/100 mmHg), with or without signs of target organ damage, emergency care will be recommended.

### Outcomes and measurements

The primary outcome is the change in systolic blood pressure levels from baseline to 12 months.

Secondary outcomes include:
−Systolic and diastolic blood pressure levels from baseline to 12 months.−Proportion of participants achieving systolic blood pressure control (<140 mmHg) from baseline to 12 months.−Changes in the prevalence of healthy behaviors (including reduced tobacco use and alcohol consumption, and regular physical activity).−Proportion of non-institutionalized individuals with hypertension (i.e., those not enrolled in cardiovascular risk management programs).−Change in cardiovascular risk score using the WHO risk prediction tools (16).−Identification of barriers and facilitators related to cardiovascular risk management.−Change in CHWs' cognitive and attitudinal competencies, assessed through knowledge, attitudes, and practices questionnaires administered to primary care health personnel.

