## Methods

### Study design

RE-HOPE will be a sequential mixed methods design study comprising two phases.

In the qualitative phase, we will conduct a study within the interpretive paradigm using a phenomenological design. Focus groups with stakeholders will be conducted using a semi-structured interview guide developed by the research team. Meetings will be held at participants' workplaces, and each session will be audio-recorded, transcribed verbatim, validated, and coded. Eligible professionals will be contacted by telephone and invited to participate voluntarily. Barriers to hypertension control identified during the formative phase, including difficulties in patient identification and challenges in coordination among health system actors affecting the delivery of cardiovascular risk programs, will be incorporated into the intervention design. Accordingly, the intervention seeks to reduce gaps in screening, improve awareness of hypertension, and strengthen healthcare professionals' knowledge of the diagnosis, treatment, and control of hypertension.

The second phase will consist of a quantitative study aimed at assessing the effectiveness of the implemented strategy. A single-arm intervention design will be used to evaluate longitudinal changes in blood pressure through within-participant comparisons of baseline and follow-up measurements.

The RE-HOPE study will be conducted in primary healthcare centers in Santander, Colombia. This manuscript describes the intervention protocol and follow-up procedures implemented by the community health team.

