### Population and sample

Adults aged ≥18 years be selected through convenience sampling from the community based on the following criteria: a) newly diagnosed hypertension (defined as blood pressure ≥140/90 mmHg); b) uncontrolled hypertension (defined as blood pressure ≥140 mmHg in individuals with a previous diagnosis of hypertension or who are currently on antihypertensive treatment); and/or c) known hypertensive individuals not regularly attending cardiovascular risk management programs at primary care centers. Exclusion criteria include established cardiovascular disease (e.g., coronary artery disease, myocardial infarction, heart failure, arrhythmias, cardiomyopathies, peripheral arterial disease, stroke or transient ischemic attack, diabetes mellitus with macrovascular complications, or history of invasive cardiovascular procedures), chronic kidney disease requiring dialysis, intolerance to antihypertensive medications, and resistant or secondary hypertension. The exclusion of these people was based on the fact that these pathologies require individualized and specialized management at high levels of care, which exceeds the capabilities of a community-based strategy.

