#### Intervention

The intervention will include the following components:

Identification of individuals with new or uncontrolled hypertension: RE-HOPE will strengthen the primary network through cardiovascular risk programs, which will promote its integration and institutionalization, a key step for the success of its implementation. In this framework, trained CHWs, supported by community leaders, will conduct active case finding in the community using a standardized screening protocol (Figure 1). Community leaders will facilitate engagement between CHWs and potential participants, organizing meetings, follow-up routes, and actions to increase access and coverage of healthcare services. Screening will occur door-to-door, during community outreach events, and at primary care facilities. After consent, individuals will undergo initial blood pressure measurement. If elevated blood pressure or another inclusion criterion is detected, a follow-up measurement will be scheduled within a week. Individuals with normal blood pressure will receive health education on healthy lifestyles and age-appropriate blood pressure monitoring recommendations (2) Those meeting hypertension criteria will be invited to participate, and informed consent will be obtained. Baseline sociodemographic and clinical data will also be collected.

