## Expected results

### Primary outcome

The primary efficacy outcome will be the change in systolic blood pressure from baseline to the 12-month follow-up visit. Based on findings from previous community-based interventions, we anticipate at least a 7 mmHg reduction in systolic blood pressure after 12 months of follow-up (8, 9).

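### Participants selected for high blood pressure are compared only with their own baseline, so regression to the mean alone could give a fall comparable to the anticipated 7 mmHg

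*Protocol article*

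**What the plan says.** Under *Study design*, "A single-arm intervention design will be used to evaluate longitudinal changes in blood pressure", by "within-participant comparisons of baseline and follow-up measurements". The stated aim of this phase is to assess the effectiveness of the strategy.

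*Population and sample* gives three routes of entry. Route (a) is "newly diagnosed hypertension (defined as blood pressure ≥140/90 mmHg"). Route (b) is a reading of at least 140 mmHg in someone already diagnosed or treated. Route (c), known hypertension without regular programme attendance, carries no blood pressure threshold.

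On repeat measurement, *Intervention* says: "If elevated blood pressure or another inclusion criterion is detected, a follow-up measurement will be scheduled within a week". It does not say whether the repeat must also be at or above 140 mmHg, or which of the two readings is baseline.

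*Outcomes and measurements* says: "The primary outcome is the change in systolic blood pressure levels from baseline to 12 months". Under *Expected results*, "we anticipate at least a 7 mmHg reduction in systolic blood pressure after 12 months of follow-up". The control target there is about 60% with SBP below 140 mmHg.

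The model under *Clinical effectiveness outcomes* is a linear mixed model with random intercepts and fixed effects for sex, region, age and anthropometry. The limitations paragraph of the *Discussion* concedes that one arm without a comparator limits attribution. It does not mention regression to the mean.

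**The concern.** A reading at or above 140 mmHg is partly the person's usual level and partly a temporary excess. Selecting on the reading selects on the excess, and the excess tends to be gone at the next visit. With a comparator, both arms would share this fall and it would cancel. Here it is added to whatever the programme achieves, always in the favourable direction.

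The mixed model does not remove it. Random intercepts describe the correlation between a person's visits, and the listed covariates adjust for who was enrolled. The contrast of month 12 with a baseline that was itself used for selection keeps the selection effect.

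At stake is the reading of the primary result. An ineffective programme could give a highly significant fall near the anticipated size, together with a visible rise in control.

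**Working it through.** **Inputs from the protocol article.** Threshold 140 mmHg; anticipated fall 7 mmHg; planning SD 50 and baseline to follow-up correlation 0.3; 1,912 participants before allowance for loss. The article gives no estimate of regression to the mean, so there is no figure to reproduce. I take 1,912 as given.

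**Assumed inputs.** The documents give no SBP mean or SD for the screened community. I assume a mean of 130 to 140 mmHg, SD 20, a 12-month correlation *r* of 0.5 to 0.7, a one-week correlation of 0.7 to 0.8, qualification on SBP, and no treatment effect.

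**One qualifying reading.** The expected fall is (1 − *r*) × (mean of those selected − community mean).
- Community mean 130: the mean among those at or above 140 is 152.8, a gap of 22.8. At *r* 0.5 the fall is 0.5 × 22.8 = 11.4.
- Community mean 140: the mean among those selected is 156.0, a gap of 16.0. At *r* 0.7 the fall is 0.3 × 16.0 = 4.8.

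**Two qualifying readings.** I simulated screening, repeat and 12-month readings as trivariate normal and required both of the first two to be at least 140.

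| Community mean | One-week *r* | 12-month *r* | Fall, one / two readings (mmHg) | Below 140 at 12 months, one / two readings |
|---|---|---|---|---|
| 130 | 0.7 | 0.5 | 11.4 / 10.4 | 47% / 39% |
| 130 | 0.8 | 0.6 | 9.1 / 8.4 | 42% / 35% |
| 130 | 0.8 | 0.7 | 6.8 / 5.6 | 36% / 27% |
| 140 | 0.7 | 0.5 | 8.0 / 7.5 | 33% / 28% |
| 140 | 0.8 | 0.6 | 6.4 / 6.0 | 30% / 24% |
| 140 | 0.8 | 0.7 | 4.8 / 4.0 | 25% / 19% |

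If one-week readings correlate no better than 12-month readings, the two-reading falls at mean 130 are lower: 8.3, 6.3 and 4.5 at *r* 0.5, 0.6 and 0.7.

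**Criterion (c).** Suppose these entrants all start below 140, with mean 130, SD 20 and *r* 0.5. Their mean is 10.2 below the community mean, so they rise by 0.5 × 10.2 = 5.1. With one qualifying reading for the others:
- 20% share: 0.8 × 11.4 − 0.2 × 5.1 = 8.1 mmHg
- 30% share: 0.7 × 11.4 − 0.3 × 5.1 = 6.5 mmHg

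The share below 140 moves the other way, from 47% to 53% and 57%, because these people began controlled.

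**Significance.** The threshold is 1.96 × SD × √(2(1 − *r*)) / √1,912. With SD 50 and *r* 0.3 it is 1.96 × 59.16 / 43.73 = 2.7 mmHg. With SD 20 and *r* 0.3 it is 1.96 × 23.66 / 43.73 = 1.1 mmHg.

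**Does using the repeat as baseline solve it?** If the repeat also selects, the two readings are interchangeable and the fall is the same from either. If it does not select, the residual is (one-week *r* − 12-month *r*) × gap. At mean 130 this is 0.2 × 22.8 = 4.6 for the pair 0.7/0.5 and 0.1 × 22.8 = 2.3 for 0.8/0.7. It is zero only if the two correlations are equal.

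**Does the one-week regression measure it?** For one qualifying reading it estimates (1 − one-week *r*) × gap: 0.3 × 22.8 = 6.8 against a true 11.4 (pair 0.7/0.5), and 0.2 × 22.8 = 4.6 against 9.1 (pair 0.8/0.6). It is a lower bound.

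**The case against.** The strongest reply is that the size rests on assumptions. That stands: the community mean and SD are not in the documents. At mean 130, a 12-month correlation of 0.7 brings the fall below 7 mmHg, and 0.8 brings it to 4.6 mmHg with one qualifying reading. People who qualify on diastolic pressure alone would regress less in SBP.

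Four stronger readings are tempting but not supported:
- **A fall of about 16 mmHg from the planning correlation of 0.3.** That value is planned for participants, whose range is cut at 140, and not for the unselected community. With mean 130 and SD 20, a community value of 0.3 gives only about 0.16 among those enrolled. An enrolled 0.3 corresponds to about 0.52 in the community, and hence 0.48 × 22.8 = about 11 mmHg on one reading.
- **Regression alone nears the 60% control target.** It reaches 57% only with a community correlation of 0.3 and a single qualifying reading. Many controlled criterion (c) entrants also bring the figure near 60%, but that is not regression.
- **A shift of setting from clinic or event to home.** The article says "Screening will occur door-to-door, during community outreach events, and at primary care facilities" and "CHWs will arrange appointments for home follow-up visits (months 1, 3, 6, 9, and 12"), so some screening is already at home, and the place of the repeat is not stated. A shift is possible, not shown.
- **The confirmatory reading as baseline removes the problem.** The working shows that it does not if that reading also selects.

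Existing safeguards deserve credit. There is a repeat within a week, one standardized measurement protocol, and the mean of the last two of three readings. Averaging within a visit reduces noise within that visit, not variation between visits.

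A condensed article may also leave the definition of baseline to the full protocol. But it does fix the outcome, the benchmark, the model and the effectiveness aim, and following those as written gives a biased estimate. The general caveat does not state the predictable direction of the bias or its size relative to 7 mmHg.

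**Conclusion.** The point holds. Entrants under (a) and (b) are selected on high pressure, judged against themselves, and analysed by a model that leaves regression to the mean in the estimate. Under the stated assumptions (community mean 130 to 140, SD 20, 12-month correlation 0.5 to 0.7, one or two qualifying readings), the no-effect fall is about 4 to 11 mmHg, comparable to the 7 mmHg anticipated. It lies on either side of that figure depending on inputs that the documents do not give, and it shrinks with the share of criterion (c) entrants, which is also not given. No-effect control among threshold entrants is about 20 to 47%, well short of 60% over most of the range. Because 1 to 3 mmHg is significant at the planned size, a significant result, or one that reaches 7 mmHg, is not in itself evidence that the strategy worked.

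**What to change.** 1. State which reading is baseline and whether it also decides eligibility. Where possible use a reading taken after eligibility is settled, not used for selection, and measured under the existing standardized protocol. Say that this reduces regression to the mean but does not abolish it.
2. Retain the screening and repeat SBP of everyone screened or re-measured, including those who fall below the threshold. Pre-specify an adjusted 12-month change beside the raw one, using the screened SBP distribution and a range of 12-month correlations. Treat the one-week screening-to-repeat regression as a lower bound only.
3. Report criterion (c) entrants without a qualifying high reading separately from threshold-selected entrants, for both the SBP change and control.
4. Name regression to the mean in the limitations, tie effectiveness wording to the adjusted range, and do not treat a raw 7 mmHg fall or 60% control as the effect of the intervention.

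The cost is a little more data retention and analysis, and a smaller headline fall. Where a post-eligibility reading is not already part of the visits, it adds one measurement. No comparator arm is needed. The retention rule should be settled before screening starts, since readings that were not kept cannot be recovered.

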**Methods:**

We describe the “Implementation, Integration, and Institutionalization of a Community-Based Care Program to Reduce Cardiovascular Risk in Santander” (RE-HOPE) study protocol. Adults aged ≥18 years, with *de novo* or uncontrolled hypertension, or with hypertension not participating in cardiovascular risk management programs, will be included. Individuals will be identified through active community screening. The intervention will consist of early identification of hypertension, enrolling participants in primary care institutions, and conducting follow-up home visits. These visits will include counseling on medication adherence and lifestyle modifications, as well as training for healthcare providers and community health workers (CHWs). Referrals to primary care providers and follow-up appointments will be coordinated by CHWs. The primary outcome will be change in BP levels from baseline to 12 months of follow-up.

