
The “Implementation, Integration, and Institutionalization of a Community-Based Care Program to Reduce Cardiovascular Risk in Santander” (RE-HOPE) study will be developed to optimize community-level hypertension management by integrating CHWs into the processes of early detection, follow-up, and blood pressure control. The RE-HOPE model combines detection and referral mechanisms, structured health counseling, ongoing monitoring, and the use of simplified clinical algorithms to facilitate therapeutic decision-making and improve clinical outcomes.

Currently, cardiovascular risk programs at both the regional and national levels have gaps that limit their coverage. First, a high proportion of individuals with hypertension are unaware of their condition and therefore do not access cardiovascular risk programs; on the other hand, although some individuals with hypertension are aware of their disease, participation in institutional activities remains suboptimal. It is estimated that compliance with institutional programs is only around 60% (11). Additionally, among those already enrolled in cardiovascular risk programs, it is necessary to overcome some of the barriers identified by users in order to achieve hypertension control, including access to health services, coverage, education about the disease, and interaction with patients (12). The RE-HOPE model is designed to address these gaps by helping institutional cardiovascular risk programs increase their coverage. This will be achieved by strengthening patient engagement, reinforcing home-based health education, and improving continuity of care through more patient-centered strategies.

The distinguishing feature of the RE-HOPE study is the timely institutionalization of patients into cardiovascular risk management programs through structured coordination between community case detection and primary healthcare providers. We aim to develop an innovative and potentially scalable strategy that, if proven effective, may help close existing gaps in hypertension control in LMICs such as Colombia.

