**Figure 1 F1:**
[figure not shown]
RE-HOPE study flowchart. Trained CHWs, supported by recognized community leaders, will conduct a door-to-door active community-based case finding using a standardized screening protocol. If hypertension is detected, a follow-up measurement will be scheduled within a week. Participants with hypertension will be referred to their assigned primary care provider based on their health insurance affiliation, using a standardized referral form. Once enrolled in a cardiovascular risk management program, home visits will be scheduled as part of the community-based intervention. BP, blood pressure; CHW, community health workers; CV, cardiovascular.

Referral to primary care providers: Participants with hypertension will be referred to their assigned primary care provider based on their health insurance affiliation, using a standardized referral form. A centralized team will submit participant lists via an online platform (e.g., OneDrive) to schedule medical appointments and ensure program enrollment. Participants and/or their families will be contacted by phone with appointment details. If a participant does not attend, they will be followed up to identify barriers and facilitate access to care. If a participant does not agree to assist, they will be excluded. Once enrolled in a cardiovascular risk management program, home visits will be scheduled as part of the community-based intervention (Figure 2).

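### The non-institutionalized outcome counts enrolment only: it is about 0% by construction in followed participants and cannot register the irregular attendance that entry criterion (c) targets

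*Protocol article*

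**What the plan says.** All places are in the protocol article.

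- **Outcome** (Outcomes and measurements): a secondary outcome is the "Proportion of non-institutionalized individuals with hypertension (i.e., those not enrolled in cardiovascular risk management programs". No denominator or time point is attached to it.
- **Entry** (Population and sample): criterion (c) covers "known hypertensive individuals not regularly attending cardiovascular risk management programs at primary care centers". It is one of three routes, joined by and/or. The Abstract puts the same group differently, as people "with hypertension not participating in cardiovascular risk management programs, will be included".
- **Pathway** (Intervention, Referral to primary care providers): a central team submits lists "to schedule medical appointments and ensure program enrollment". Then: "Once enrolled in a cardiovascular risk management program, home visits will be scheduled as part of the community-based intervention". The Figure 1 legend repeats this order. On those who do not come along, the text says: "If a participant does not agree to assist, they will be excluded".
- **Rationale** (Introduction): the gap is described partly as one of participation, since "although some individuals with hypertension are aware of their disease, participation in institutional activities remains suboptimal". The text goes on to barriers among people who are already in a program, and names timely institutionalization as what distinguishes the study.
- **Nearest attendance measure** (Table 1, Implementation phase): the Reach indicator is the percentage of screened hypertensive individuals who attend a primary care appointment, taken from the referral tracking system.

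**The concern.** Three words are used for nearly the same idea: participating (Abstract), regularly attending (entry criterion) and enrolled (outcome). Someone can be enrolled and not attend, and the Introduction itself recognizes problems among people already enrolled. The outcome therefore does not measure the state that brings a criterion (c) participant into the study.

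The pathway makes this worse. Enrolment is a step the team carries out before the first home visit. An outcome defined as non-enrolment is thus settled before follow-up starts for everyone who is followed. The study has one arm, so the before-after contrast is all there is. A fall in the non-institutionalized share could be read as an effect on engagement with care when part of it only restates the rule for scheduling visits.

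**Working it through.** The article states no target, power or sample size for this outcome, so there is no figure to reproduce. The check sets the definitions against the pathway and then follows the outcome under each possible denominator.

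**1. Who can change on the outcome?**

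| Status at entry | Scored at baseline | Scored once home visits begin | Change possible? |
|---|---|---|---|
| Not enrolled (for example newly diagnosed) | Non-institutionalized | Institutionalized, by the visit rule | Yes, but fixed by the pathway |
| Enrolled, not attending regularly (eligible under (c)) | Institutionalized | Institutionalized | No |
| Referred, never enrolled | Non-institutionalized | No home visits | Only if kept in the denominator |

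**2. The outcome by denominator.** Let *e* be the share of referred people who enrol, *d* the share who decline and are excluded, and *a* the share of enrolled people who attend regularly.

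- Followed participants: every one has been enrolled, so the outcome is 0 for any *a*, apart from later disenrolment.
- All referred people, decliners kept: the outcome is 1 − *e*. It also does not depend on *a*.
- All referred people, decliners removed: the outcome is (1 − *e* − *d*)/(1 − *d*). This is below 1 − *e* whenever *e* and *d* exceed 0, because (1 − *e*)(1 − *d*) = 1 − *e* − *d* + *ed*. If everyone who fails to enrol is a decliner (*d* = 1 − *e*), it falls to 0.
- Share not in regular program care among all referred: 1 − *e* × *a*.

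**3. Illustration with assumed values.** Neither *e* nor *a* is given in the article, so the range is shown.

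| *e* | Outcome, followed | Outcome, all referred (1 − *e*) | Not in regular care, *a* = 0.40 | *a* = 0.60 | *a* = 0.80 |
|---|---|---|---|---|---|
| 0.60 | 0% | 40% | 76% | 64% | 52% |
| 0.80 | 0% | 20% | 68% | 52% | 36% |
| 0.95 | 0% | 5% | 62% | 43% | 24% |

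For *e* = 0.80 and *a* = 0.60, for example, 1 − 0.80 × 0.60 = 0.52. With *e* = 0.80, removing decliners moves the outcome from 20% (*d* = 0) towards 0% (*d* = 0.20). The table shows only that the outcome stays the same across a row while attendance varies. It does not predict what this cohort will do.

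**4. Does another stated measure fill the gap?** The Reach indicator counts attendance at an appointment after screening. That is a first contact, not regular attendance, and it has no value at entry to compare with. The Table 1 indicators on visit completion concern home visits by community health workers, not program attendance.

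**The case against.** The best defence is that enrolment is what the article means by institutionalization. Table 2 gives health workers the function of institutionalizing the person and lists enrolment among the activities, and the Introduction speaks of bringing patients into programs and raising coverage. An outcome need not use the same measure as an entry criterion, and people entering by routes (a) and (b) from outside a program can show a real change in enrolment. The outcome also refers to individuals with hypertension, where the item on blood pressure control refers to participants, so a coverage reading over everyone identified is open. A condensed article may leave the denominator to the full protocol. All of this stands: enrolment is a legitimate outcome, and the unstated denominator is not in itself a fault.

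Two stronger readings are tempting, and the article does not support them. A reader might infer that the study cannot show whether the care gap closed. That goes too far: with all referred people as denominator the outcome can describe the coverage part of the gap, and Reach adds attendance at an appointment. A reader might also take the Introduction's sentence, "It is estimated that compliance with institutional programs is only around 60" per cent, and conclude that about 40% (1 − 0.60) would be hidden non-attenders. That figure is an undefined background estimate. It is not stated to be attendance among enrolled people, and using it here would assume that the intervention leaves attendance unchanged. It can serve only as one value in an illustration.

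The defence does not reach the core of the point. Under either denominator the measure is blind to regular attendance, and the exclusion sentence could remove from the count some of the people it is meant to count.

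**Conclusion.** The point holds in a limited form. Computed in followed participants, the outcome is about 0% by construction, and enrolled non-attenders admitted under (c) contribute no change. Computed in all identified people with hypertension, it describes enrolment coverage but not regular attendance, and no other stated measure gives attendance at both entry and month 12.

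This rests on reading the visit rule as the text and the Figure 1 legend state it, and on little later disenrolment. The effect on the study's result cannot be quantified: the article gives neither the number of criterion (c) entrants already enrolled nor an attendance rate for this cohort. The primary outcome is not touched. The change is still worth making, because this secondary outcome bears on the feature the article presents as the study's distinguishing one.

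**What to change.** 1. **Enrolment as a coverage measure.** Compute it in all consented, referred people with hypertension. Count those who decline or never enrol as non-institutionalized rather than excluding them from this measure. Consent and baseline data come before referral in the described sequence, and the referral tracking system is already planned. This concerns the count only, not who receives home visits.
2. **Attendance as an added measure.** Record program attendance at baseline and month 12, defined as for criterion (c), by a question at the existing baseline and month-12 contacts and from provider records where available. The study team sets the look-back window and uses the same one at both times.
3. **Wording.** Reconcile the Abstract, Population and sample, and Outcomes and measurements, so that participating, attending and enrolled are either one defined term or clearly separate ones.

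The cost is one extra data item at two time points. Provider records are not a free source for it: Data collection currently takes only laboratory results from them, which is why the question to participants is needed. The institutionalization figure will also look less favourable.
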